#### Exploratory outcomes

Change in HbA1c—number of patients previously in diabetic HbA1c range, now in ‘at risk of diabetes’ (6%–6.4%) or ‘diabetes in remission’ (<6.0%, off medications) HbA1c range.Change in fasting glucose, fasting insulin, Homeostasis Model Assessment steady state beta cell function (HOMA-%B) and insulin sensitivity (HOMA-%S).Change in weight.Change in diabetic medication (number of diabetic medications currently prescribed to the patient; dose of diabetic medications; initiation of new medication during study period; initiation of insulin; initiation of injectable diabetic medication; number of medications stopped or changed during the study period).Change in lipid profile—total cholesterol, high-density lipoprotein (HDL), triglycerides, calculated non-HDL cholesterol and total cholesterol:HDL ratio.Change in liver function tests (bilirubin, alanine aminotransferase (ALT), aspartate aminotransferase (AST), alkaline phosphatase (ALP), albumin, AST:ALT).Change in BP (systolic, diastolic).Change in antihypertensive medication (number of medications started and stopped during study period; dose of antihypertensive medications; initiation of new medication during study period).Change in medication prescribing costs (total and diabetic) across study group and total practice diabetic population.Effect on patient’s Problem Areas in Diabetes (PAID) score.

#### Qualitative measures

Experience of and acceptability of the intervention, for patients and healthcare practitioners (assessed using qualitative focus groups following completion of the initial study period).

### Measurements

Figure 2 provides a summary of the measurements collected.

**Figure 2 F2:**
[figure not shown]
Schedule of measurements. DIAMOND, Dietary Approaches to the Management Of type 2 Diabetes.

### Sociodemographic characteristics

Participants will be asked to self-report age, sex and ethnicity, education history and employment status.

### Medical and medication history

Relevant medical history and all current medication will be recorded and checked against the participant’s medical record.

### Physical measurements

Height will be measured using stadiometers, to the nearest 1 cm. Weight will be measured to the nearest 0.1 kg using a digital scale (SC-240 MA, Tanita Japan). BMI will be calculated using the standard formula BMI=weight(kg)/height(m).^2^ BP will be measured in triplicate after 5 min seated rest, with at least 1 min between each measurement. All assessors will be trained in standardised methods of taking physical measurements according to the study manual of procedures.

### Fasting blood sample

A fasting venous blood sample for HbA1c, fasting insulin, fasting glucose, liver function tests (bilirubin, ALT, AST, ALP, albumin) and lipid profile (total cholesterol, triglycerides, HDL, calculated low-density lipoprotein (LDL) and total:HDL cholesterol ratio) will be collected at baseline, 8 weeks and 12 weeks. All blood samples will be taken, handled, analysed and disposed of according to standard NHS procedures and local practice policy.

### Questionnaires

During study follow-up visits, patients will be asked to complete questionnaires to assess the following measures:*Quality of life:* the PAID score, a 20-item questionnaire measuring problems related to emotions, treatment, food and social support,^33^ will be measured at baseline and 12 weeks.*Dietary composition:* a 24-hour dietary recall questionnaire will be used to assess intake of different food groups at baseline, 2, 8 and 12 weeks.*Motivation:* self-reported motivation and perceptions across domains of diet, health and diabetes control will be assessed using a 6-point questionnaire at baseline and 12 weeks.*Self-reported adherence to intervention:* self-reported adherence to the three core components of the dietary intervention will be assessed at 2, 4, 8 and 12 weeks.

### Retention and withdrawal

Each participant will have the right to withdraw from the study at any time. In addition, the investigator may discontinue a participant from the study at any time if they consider it necessary for any reason, including ineligibility (either arising during the study or having been overlooked at screening). If a participant requests to withdraw from the study, it will be explained to them that we would like to use their data collected up to the point at which they have withdrawn from the study, unless they request that we do not do so. The reason for withdrawal will be recorded in the case report form (CRF). Withdrawn participants will not be replaced in this feasibility study. To reflect the burden of participation and promote participant retention and complete follow-up, participants will be offered a £20 gift card on attending the 12-week follow-up appointment.

### Adverse events

We will record and report all SAEs following Good Clinical Practice and standard Health Research Authority (HRA) processes. The duration of the SAE recording period for each participant lasts from their enrolment on to the study, to their completion of the study. We elected not to record other adverse events (AEs) because this process is burdensome for clinicians and participants, and we considered that this programme was unlikely to induce significant AEs.

### Data management

Data will be recorded on hard copy CRFs and subsequently entered into a web-based data-capture system (RedCap, 2018 Vanderbilt University) with data stored on a secure server hosted by the Primary Care Clinical Trials Unit at the University of Oxford. The system has an inbuilt audit trail facility and ability to run internal validation checks.

### Statistical analysis

Primary outcome measures for this study are progression criteria, to inform any future RCT powered to detect an intervention effect. Analysis for progression criteria will use data from all participants recruited to the trial. Descriptive statistical methods along with inferential statistics presenting CIs will be used to analyse and report progression criteria.

Secondary outcome measures for this study include process measures and exploratory effectiveness measures. Both measures will use all collected data, including that from participants who have not completed the trial, and from participating practices (where pertaining to proportions of patients identified as eligible, and responding to invitations to participate). Descriptive comparative summary statics (eg, difference in means or proportions, together with 95% CIs, comparison with baseline and overall change compared with control group) will be used.

Acceptability and experience of the intervention by participants and healthcare professionals will be collected as qualitative data from interviews and focus groups conducted after intervention completion. These data will be qualitatively analysed using thematic analysis, and reported descriptively.

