### Sample size

The total number of participants recruited for this study will be 30. As this is a feasibility study, it has not been powered to detect a statistically significant difference in efficacy between the arms. In determining thresholds for progression criteria, based on previous trials of a similar nature, we expect at least 75% achievement.^27 28^ If so, the 95% CI will exclude 60%, and therefore we have set this as the progression criteria for each criterion, requiring a sample size of 30 participants allocated in a 2:1 ratio, intervention:control.

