### Randomisation

All eligible, consenting participants will be randomised to one of the two trial arms (intervention or control), using permuted block design randomisation with blocks of 3 and 6. Allocation will be stratified by practice. An independent researcher will generate the set of sequences and assign participants to the intervention groups using sequentially numbered sealed envelopes to ensure allocation concealment until interventions are assigned. Due to the nature of this study, it will not be possible to further blind participants, clinicians or some of the study team to the treatment allocation beyond this point.

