#### Secondary

A mixture of quantitative and qualitative methods will be used to assess process measures and effectiveness measures. This feasibility study is not powered to detect statistical differences in efficacy outcomes but will examine the following parameters in order to test trial procedures, process, resources and management, to aid sample size estimates for a future trial, to determine the most appropriate primary outcome measures for a future trial and to inform further development of the intervention strategy.

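### The between-arm summaries named for the continuous exploratory outcomes are unadjusted; adding baseline as a covariate would protect against chance imbalance with 20 v 10 and modestly sharpen HbA1c

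*Protocol article*

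**What the plan says.** The Statistical analysis section of the protocol article says that process and exploratory measures will be reported with descriptive comparative summaries. In brackets, introduced by eg, it lists "difference in means or proportions, together with 95% CIs, comparison with baseline and overall change compared with control group". No model and no covariate is named, and none is ruled out.

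Four other places bear on the point:

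- **Baseline data.** Under Participant flow, baseline measurements are taken before randomisation and all outcome measures are repeated at 12 weeks. The Fasting blood sample section has HbA1c at baseline, 8 and 12 weeks.
- **Size and split.** Sample size states that "The total number of participants recruited for this study will be 30", in a 2:1 ratio. It adds that "it has not been powered to detect a statistically significant difference in efficacy between the arms".
- **Stratification.** Under Randomisation, "Allocation will be stratified by practice". Recruitment gives two to four practices.
- **Use of the results.** The Secondary outcomes section says these measures are examined, among other reasons, "to aid sample size estimates for a future trial" and to help choose its primary outcome.

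The Exploratory outcomes section words nearly every item as a change. For HbA1c it spells this out as a count of patients moving between glycaemic categories.

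**The concern.** A comparison of change from baseline assumes that each unit of baseline carries through in full to follow-up, a slope of 1. If the true slope is lower, as is usual for a variable laboratory measure, the change score over-corrects for any baseline difference between arms. With only 10 controls, sizeable chance differences are likely. Analysis of covariance estimates the slope from the data, so it removes this error in expectation and usually leaves less residual variance.

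What is at stake is the quality of the HbA1c and similar estimates that this study hands to the planners of a full trial. No decision rule of the feasibility study depends on them.

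**Working it through.** **Inputs from the protocol article.** N = 30 and ratio 2:1 (Sample size), hence 20 v 10. Practices: 2 to 4 (Recruitment).

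**Assumptions.** The article gives no SD and no baseline-to-follow-up correlation r for any exploratory outcome. I take equal SDs at both times, vary r, assume complete follow-up, and express results in units of the outcome SD.

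**The plan's own figure.** There is none on this point. The number 30 is justified through the progression criteria alone. At exactly 75%, the Wald interval for n = 30 is 0.75 ± 1.96 × √(0.75 × 0.25/30) = 59.5% to 90.5%, which does not exclude 60%. That is a separate matter; here 30 is only an input.

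**Step 1: chance imbalance at baseline.**

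- SE of the difference in baseline means = √(1/20 + 1/10) = √0.15 = 0.387 SD.
- P(|difference| > 0.5 SD) = 2 × [1 − Φ(0.5/0.387)] = 0.20.

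**Step 2: what an imbalance does to a change score.** For a baseline difference d, the expected shift in the estimate has size (1 − r) × d. With d = 0.5 SD:

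| r | shift (SD) | share of the change-score CI half-width |
|---|---|---|
| 0.5 | 0.25 | 0.25/0.793 = 32% |
| 0.7 | 0.15 | 0.15/0.615 = 24% |
| 0.9 | 0.05 | 0.05/0.355 = 14% |
| 0.95 | 0.025 | 0.025/0.251 = 10% |

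**Step 3: width of the 95% CI.**

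- Change score: half-width = t(28) × √[2(1 − r)] × √0.15.
- Analysis of covariance on baseline: half-width = t(27) × √(1 − r²) × √[0.15 × (1 + 1/26)]. The factor 1 + 1/26 is the expected price of estimating the slope in 30 patients.
- Example at r = 0.5: change score 2.048 × 1 × 0.387 = 0.793; covariance 2.052 × 0.866 × 0.395 = 0.701.

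| r | change score | covariance | difference in width |
|---|---|---|---|
| 0.3 | 0.939 | 0.773 | −18% |
| 0.5 | 0.793 | 0.701 | −12% |
| 0.7 | 0.615 | 0.578 | −6% |
| 0.8 | 0.502 | 0.486 | −3% |
| 0.9 | 0.355 | 0.353 | about 0 |
| 0.95 | 0.251 | 0.253 | +1% |

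The change score is the comparator because the outcomes are listed as changes. A plain difference in 12-week means would have a half-width of 0.793 at every r.

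**Step 4: practice.** Adding one to three practice terms to the covariance model alters the half-width by less than 1% by formula (at r = 0.5, from 0.701 to at most 0.705). Simulation with blocks of 3 and 6 within two or four practices, 3,000 runs per scenario, gave a change in width of about −1% to +2%.

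**Step 5: validity of the unadjusted interval.** In the same simulations the unadjusted change-score CI covered the true value in 94% to 96% of runs in every scenario, including one with a practice intraclass correlation of 0.05.

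**The case against.** The strongest reply is that the list is illustrative and labelled descriptive, in a journal article whose analysis plan is not shown. A reader might infer that the trial has decided against adjustment. The text does not support that: it names no model and excludes none. What stands is narrower: every between-arm summary it does name is unadjusted.

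Other stronger readings also fail:

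- **That the planned estimates are biased or their intervals invalid.** Over repeated randomisation the unadjusted estimate is unbiased, and coverage was nominal. The shift in Step 2 is conditional on the imbalance that happens to occur in this one randomisation.
- **That unadjusted intervals are wider throughout.** At r of about 0.9 or more, plausible for weight over 12 weeks, the lost degree of freedom and the cost of estimating the slope cancel the gain.
- **That leaving out practice makes the interval too wide.** Practice terms change the width very little, and stratified blocks already limit imbalance between practices.
- **That the full trial will be sized wrongly.** Baseline and 12-week values will be on file, so the residual SD and the correlation can be computed whatever table is printed. A change-score SD would also err towards a larger trial.

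Two further points stand. HbA1c is also defined by category counts, to which a linear model does not apply. And these outcomes are exploratory in a trial that claims no power for efficacy.

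**Conclusion.** The point holds as a modest improvement to the continuous exploratory outcomes. At an assumed r of 0.5 to 0.7, plausible for HbA1c, baseline adjustment narrows the CI by roughly 6% to 12%. It also removes, in expectation, a shift of 0.15 to 0.25 SD should the arms differ by 0.5 SD at baseline; a difference larger than that has about a one in five chance. For weight, no gain in width should be expected.

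These sizes rest on correlations that the article does not give, on equal SDs at both times, and on all 30 patients being followed up. The three progression criteria, and so the decision whether to proceed, are not affected.

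**What to change.** Add a sentence to the Statistical analysis section, or confirm that the analysis plan already contains it: for each continuous exploratory outcome, the 12-week difference between arms will be estimated with a 95% CI from a linear model with arm and baseline value. Practice, as the stratification factor, may be added, but little precision should be expected from it.

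Report the residual SD and the baseline-to-follow-up correlation for each outcome, since these are what the full trial's sample size calculation needs. Keep raw means and changes by arm, and the HbA1c category counts, as description.

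No new data are required. The cost is one degree of freedom for baseline, plus one to three if practice is included.

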### Patient involvement

This study evolved through patient demand in the local area, to know more about dietary options and in particular low-carbohydrate diets for people with type 2 diabetes. We convened two panels of patients with type 2 diabetes, one consisting of members who had recently tried variations of a low-carbohydrate, low-energy diet, to inform and advise on the dietary and behavioural support components of the intervention, the patient materials and the perceived benefits or burdens of the study for patients. One patient member has subsequently joined the trial management group and will be involved in trial steering decisions during the monitoring and running of the trial, and regarding progressing to a full-scale trial.

### Qualitative substudy

The purpose of the nested qualitative sub-study is to explore patients’ and healthcare professionals’ experience of receiving, enacting and delivering this intervention, and of participating in the study. We will seek the views of up to 10 patient participants from the intervention group, from those who consent to be contacted for the nested qualitative study, and 6–8 healthcare professionals. The patient participants chosen will aim to reflect a range of success with weight loss and glycaemic control, with thought given to not mixing those who have found the programme easy or successful, with those who have not achieved their goals. Additionally, we will aim to capture a breadth of participant characteristics (age, gender, social class, ethnicity or, for the healthcare professional interviews, the participant’s profession). All healthcare professionals who have been involved in the study will be invited to take part. Should more participants volunteer than are required, purposive sampling will be used to ensure both GPs and nurses are represented in the cohort, and to include those who have conducted a greater number of sessions.

Focus groups will be conducted after all participants have completed their 3-month study follow-up period. Written informed consent will be taken before the focus group commences. All focus groups will be audio recorded, and these audio-recordings will be transcribed. Patients will be reimbursed for their time and practices will be reimbursed for the healthcare professionals taking time out from their clinical duties to participate.

Focus groups will follow broad topic areas based on the study objectives, but will encourage participants to discuss their perceptions and experiences freely and in depth. Topics will include: the acceptability of the intervention; views on which components of their treatment group they felt were effective and which were not effective; thoughts about impact on experience of diabetes and its management; thoughts about weight management going forwards. Data will be analysed using thematic analysis.

## Ethics and dissemination

Any protocol modifications will be submitted for review by the research ethics committee and amended at the trial registry.

If the trial proves feasible, according to the specified progression criteria it is planned that the results will inform design of a full-scale randomised trial to test the efficacy of the intervention to improve glycaemic control.

The findings of this feasibility study will be submitted for publication in a peer-reviewed journal, and presented at conferences, to disseminate the results to academic and health professional audiences, and made available to participants and to a wider public on our website at the time of publication.
